### Randomisation

Participants are randomised to the intervention or control group by the RO using an automated Interactive Voice Response System (IVRS) located at the National Health and Medical Research Council Clinical Trials Centre (NHMRC CTC), Sydney, Australia. The IVRS, accessible by telephone, uses a computer-generated randomisation sequence, enabling immediate 1:1 allocation to unblinded treatment groups. Participants and health service and WSU staff are not blinded to treatment allocation due to the nature of the intervention. Randomisation is stratified using permuted block design (block size 4), based on participating site, child age (3 to 5 years versus 6 to 16 years), and whether unilateral or bilateral OME at presentation. These strata were determined a priori given their potential association with effectiveness.

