### Study population/eligibility criteria

Aboriginal or Torres Strait Islander children, attending urban or regional Aboriginal Health Services, aged 3–16 years with unilateral or bilateral type B tympanograms are eligible for inclusion. Tympanometry is conducted by a trained research officer (RO), and eligibility, including trace type, is confirmed by the treating General Practitioner (GP). Exclusion criteria include clinical confirmation of a current acute upper respiratory infection, acute otitis media, perforated tympanic membrane, or ventilation tube in situ; ear surgery booked within 1 month of diagnosis; self-reported latex allergy, recent nosebleed (at least 1 nosebleed in last 3 weeks or > 1 nosebleeds in last 6 months); self-reported or documented history of an at-risk condition (e.g., immunosuppression); previous participation in the trial; or self-reported inability to use the autoinflation device (demonstrated by the inability to blow nose).

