### Follow-up (visits/assessments/measures/tools)

Follow-up (Fig. 1) by the RO occurs via phone at day 3 and weekly from weeks 1–3 and 5–11 and at Aboriginal Health Services at 1, 3, and 6 months post-enrolment and randomisation (day 0). Data sources, the findings of which are recorded on trial-designed paper source document worksheets, include tympanometry, video pneumatic otoscopy, audiometry, adherence and cost-effectiveness progress questions, an OMQ-14 quality of life questionnaire [35], nasal autoinflation adherence diary, and qualitative interviews. Medically trained CIs review participant medical records for additional information related to ear disease and treatment including adverse events, health care utilisation, and medication usage, for up to 6 months post-randomisation. This information informs determination of secondary outcomes including the cost-effectiveness analysis. Details of data collection at each of the scheduled assessment times are summarised in Table 1.

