### Data management

Source data is captured either in password-protected participant electronic medical record databases, on trial-designed paper source document worksheets, or diagnostic device paper or electronic software output. Paper source documents are stored in a lockable cabinet, and electronic source documents in password-protected health service databases, accessible to authorised health service staff only. Source data is de-identified and coded using randomisation number before it is single entered by the RO into an encrypted, password-protected validated electronic Case Report Form database (Medrio™) hosted in the USA. De-identified, coded data is accessible to authorised health service and WSU staff only. Qualitative interviews are taped and transcribed, then electronic copies de-identified and coded using randomisation number, for storing by WSU. Paper and electronic source data will be securely archived by health services, and de-identified, coded data, by WSU, for a minimum of 15 years after completion of the trial.

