### Data monitoring

All data collected from the first patient recruited at each participating site are reviewed for accuracy and validity. Consent, eligibility, primary outcome data points, serious adverse events, and select adverse events of interest are monitored for all participants. All remaining data are randomly monitored (estimated 10% of participants) for quality assurance purposes.

INFLATE is a low-risk trial using the nasal autoinflation device within its marketed indication and population. Given the low-risk nature of the trial, the use of ongoing centralised statistical and on-site monitoring, and ongoing site and WSU staff training, an external audit will not be conducted.

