##### Adherence to treatment

ROs will telephone parent/carers at day 3 and weeks 1–3, and 5-11 post treatment allocation, or offer a clinic of home visit, to support correct nasal balloon autoinflation technique, capture adherence data, and promote ongoing treatment adherence. Participants additionally complete a take-home daily autoinflation adherence diary, by placing a sticker in the diary each time the device is used. Reported treatment adherence will be the percentage of maximum treatment adherence for the treatment period.

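### The 1-month tympanogram type that decides the primary outcome is read by staff who know the arm; deriving it by a fixed, arm-independent rule would cheaply reduce the risk of bias

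*Protocol article*

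**What the plan says.** The trial is declared open-label. Under Randomisation the article says that "Participants and health service and WSU staff are not blinded to treatment allocation due to the nature of the intervention".

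The research officer (RO) role appears at each step that leads to the primary outcome:

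- **Allocation** (Randomisation): "Participants are randomised to the intervention or control group by the RO using an automated Interactive Voice Response System (IVRS").
- **Testing** (Study population/eligibility criteria): "Tympanometry is conducted by a trained research officer (RO), and eligibility, including trace type, is confirmed by the treating General Practitioner (GP"). This sentence concerns eligibility.
- **Follow-up** (Follow-up section): the RO's contacts include the 1-month clinic visit and two later ones. The text reads "by the RO occurs via phone at day 3 and weekly from weeks 1–3 and 5–11 and at Aboriginal Health Services at 1" (month).
- **Coaching** (Adherence to treatment): ROs telephone or visit families "to support correct nasal balloon autoinflation technique, capture adherence data, and promote ongoing treatment adherence".
- **Data entry** (Data management): source data are coded by randomisation number and "single entered by the RO into an encrypted" database.

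Two further statements bear on the remedy. Data management lists "diagnostic device paper or electronic software output" as one of several forms that source data may take. Data monitoring says that consent, eligibility, "primary outcome data points, serious adverse events, and select adverse events of interest are monitored for all participants".

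The primary outcome is binary and depends wholly on tympanogram type at 1 month: type A or C1 counts as improvement and C2, C3 or B does not, with a further condition on the contralateral ear in unilateral cases.

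**The concern.** The reason given for not blinding is the nature of the intervention. That explains why the child, the family and the coaching staff must know the arm. It does not explain why a recorded trace must be classified with the arm known.

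Tympanometry is an instrument measurement, so the room for judgement is narrower than with a symptom score, but it is not nil. The background box on tympanometry describes the types by shape and in words, without numeric cut-offs, and calls C2 and C3 equivocal. The primary outcome places its cut between C1 and C2, where one call turns a non-improved child into an improved one.

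If borderline calls depend on the arm, the error is differential. It then shifts the estimated relative risk and the false-positive rate, and neither the planned covariate adjustment nor multiple imputation can correct it. Error that does not depend on the arm would leave the type I error at its nominal level and cost only power.

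**Working it through.** **Step 1. Who could classify the 1-month trace?** The RO is the stated tympanometry operator at eligibility and the stated conductor of the 1-month visit. The GP is the only other reader mentioned, for eligibility. Both are health service staff and so unblinded. Under Treatment groups, whether an intervention child continues the device after 1 month depends on the tympanogram type, which implies a reading on site with the arm known. The article describes no masked reader.

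**Step 2. Reproduce the design.** Inputs from Sample size and power: 35% v 50%, 80% power, 5% significance. With a two-sided test, pooled variance under the null and no continuity correction:

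n = [1.960·√(2·0.425·0.575) + 0.842·√(0.35·0.65 + 0.50·0.50)]² / 0.15² = 169.3, so 170 per arm and 340 in total. Power at 170 per arm is 80.2%, and 340/0.85 = 400. The stated figures reproduce, so the same test can be used below.

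**Step 3. Effect of arm-dependent reading when there is no true effect.** Let f be the share of truly non-improved intervention children read as improved. This share is an assumption. The control arm is read correctly.

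- Control proportion: p₁ = 0.35.
- Apparent intervention proportion: p₂ = 0.35 + 0.65·f.
- d = p₂ − p₁ and p̄ = (p₁ + p₂)/2.
- SE₀ = √(2·p̄(1−p̄)/170) and SE₁ = √([p₁(1−p₁) + p₂(1−p₂)]/170).
- P(reject) = Φ((d − 1.960·SE₀)/SE₁) + Φ((−d − 1.960·SE₀)/SE₁).

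Example with f = 5%: p₂ = 0.3825, d = 0.0325, SE₀ = 0.0523, SE₁ = 0.0522. P(reject) = Φ(−1.339) + Φ(−2.583) = 0.095.

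| f (assumed) | Children misread, 170·0.65·f | False difference (points) | Apparent RR | Two-sided type I error |
|---|---|---|---|---|
| 0 | 0 | 0 | 1.00 | 5.0% |
| 1% | 1.1 | 0.65 | 1.02 | 5.2% |
| 2% | 2.2 | 1.3 | 1.04 | 5.7% |
| 5% | 5.5 | 3.3 | 1.09 | 9.5% |
| 10% | 11.1 | 6.5 | 1.19 | 23.4% |

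At 1% to 2% the inflation is slight. At 10% the false difference is 6.5/15 = 43% of the target effect.

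**Step 4. Contrast with error that ignores the arm.** If a share e of children is misread in each direction in both arms, the proportions are 0.35(1−e) + 0.65e in the control arm and 0.50 in the intervention arm. Type I error stays at 5%. Power falls from 80.2% to 76.8% at e = 2% and to 71.1% at e = 5%.

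**The case against.** The strongest case on the other side has five parts.

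- **The classifier is not named.** No sentence says who types the 1-month trace, and the tasks belong to a role. A reader might infer that one individual officer randomised, coached, tested and typed the same child. The article does not show this. What stands is that the roles it describes all know the arm.
- **The article is condensed.** Retest rules and numeric cut-offs may be in the full protocol or a manual, and a reader outside the health services and WSU is not expressly excluded. That is fair, and their absence from the article is not the point. The point rests on the stated lack of blinding of all health service and WSU staff.
- **Direction and size are assumed.** A reader might infer that the result will be biased in favour of the device. The documents do not support that certainty. The measure is an instrument trace, no misreading rate is given, and because a type B reading at 1 month leads to continued use, staff incentives need not all run one way. Bias towards the device is plausible in an open-label trial, but not established.
- **Masked monitoring is not free.** A reader might infer that the planned check of every primary data point already offers a masked second reading. WSU staff are unblinded, and access to coded data is limited to authorised health service and WSU staff. A randomisation number does not mask someone who knows the allocation, so arm-hidden monitoring needs a person without allocation access.
- **Retention of output is not shown for every ear.** Device output is one of several listed forms of source data, and the Follow-up section has findings recorded on paper worksheets. Back-entry may be incomplete.

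These objections narrow the claim and the remedy. They do not supply a reason for leaving classification to an unmasked reader when a fixed rule could do it.

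**Conclusion.** The point holds as a risk of bias. As described, the primary outcome depends on an on-site reading by staff who know the arm, and the reason given for open-label conduct does not extend to classifying a recorded trace. The size is unknown. With no true effect, 35% improved and 170 per arm, type I error runs from 5.2% at 1% one-directional misreading to 23.4% at 10%. This assumes that only non-improved intervention children are misread and that controls are read correctly. The sample size is not affected: 340 evaluable and 400 randomised stand. The change is worth making because it is cheap relative to what it protects.

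**What to change.** 1. Add eCRF fields for the tympanometer's numeric values for each ear at each visit (peak pressure, compliance, canal volume).
2. Write down the numeric cut-offs for each type, and derive the type by a pre-specified program that does not use the arm.
3. State that the first technically valid trace at the visit counts.
4. Use the derived type for the primary analysis and the on-site reading as a sensitivity analysis. On-site readings continue to guide care unchanged.
5. Back-enter earlier visits only where device output was kept, and report how many were recovered. With 137 of 400 children randomised by January 2022 (Trial status), 400 − 137 = 263 of the planned sample were still to be recruited at that date.
6. Optional: if existing personnel without allocation access can carry out the planned monitoring of primary data points, hide the arm during it. The fix does not depend on this.

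The cost is a few eCRF fields, a short program and some back-entry, with no extra reader, visit or procedure. The change removes the reader's discretion at the boundary between A/C1 and C2/C3/B. It does not remove all risk, because an unblinded officer still runs the test, judges whether a trace is valid and enters the values. The trial report should say so.

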### Screening/enrolment

Aboriginal Health Services are funded to recruit research officers (ROs) who, with GPs and other health care providers, identify potential participants by reviewing existing health service clinical databases and medical records for children with past and/or current OM. Treating clinicians or their delegate then contact a child’s parent/carer via phone or mail to inform them about the trial and assess their interest in participating. Children of interested parent/carers are invited to attend the health service for formal screening and confirmation of eligibility. Research officers, GPs, and other health care providers also opportunistically screen all children visiting Aboriginal Health Services regardless of the reason for attendance, and at school ear screenings and community health promotion events and, if found eligible, formal screening is offered to confirm eligibility. Children are considered enrolled where eligibility is confirmed by a GP and written informed consent to participate is obtained. Randomisation and baseline assessments are conducted immediately following enrolment (day 0).

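### A single, published block size of 4 in an open-label trial lets the research officer who recruits and randomises know some allocations in advance

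*Protocol article*

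**What the plan says.** The Randomisation section of the protocol article fixes one block size: "Randomisation is stratified using permuted block design (block size 4), based on participating site". The remaining stratification factors are "child age (3 to 5 years versus 6 to 16 years), and whether unilateral or bilateral OME at presentation", so each site runs four separate sequences. No variation in block size is stated, nor that the size is withheld from sites.

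The same section says "Participants are randomised to the intervention or control group by the RO", through a central automated telephone system, "enabling immediate 1:1 allocation to unblinded treatment groups". It adds: "Participants and health service and WSU staff are not blinded to treatment allocation due to the nature of the intervention".

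The RO role also comes in before randomisation. Under Screening/enrolment, "Aboriginal Health Services are funded to recruit research officers (ROs) who, with GPs and other health care providers, identify potential participants". Under Study population/eligibility criteria, the RO performs the tympanometry and the treating GP then confirms eligibility, including the trace type. Under Screening/enrolment, GP confirmation and written consent precede randomisation.

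The article appeared on 14 April 2022. Trial status gives 137 of 400 children randomised as at January 2022, and recruitment scheduled to stop on 31 December 2022.

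**The concern.** A central telephone system hides the list. It does not hide what follows from past allocations once the block size is known and every past allocation in the stratum has been seen. With 1:1 blocks of exactly 4, the last place in a block is always determined, and the third is determined whenever the first two went to the same arm. The RO knows a child's age group and laterality before calling, and so knows which sequence applies.

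Foreknowledge matters most before consent: whom to approach first, how warmly to encourage a family, when to book formal screening. If children with a better outlook are steered towards one arm, the comparison of 1-month improvement is biased. The planned adjustment for age, sex, laterality and site deals with that only so far as the steering runs through those factors.

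**Working it through.** **The plan's own figure.** The block size is a stated rule, so there is no calculation to reproduce. The sample size is not in dispute. With 35% against 50%, two-sided 5% and 80% power, n per group = [1.96·√(2·0.425·0.575) + 0.842·√(0.35·0.65 + 0.50·0.50)]² / 0.15² ≈ 169.3, so 170. Then 340/0.85 = 400. Both agree with the article.

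**Predictability in a complete block of 4.** There are 6 equally likely orders of two A and two B.

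| Position | Known with certainty | Best guess correct |
|---|---|---|
| 1 | 0 | 1/2 |
| 2 | 0 | 2/3 |
| 3 | 1/3 | (1/3)·1 + (2/3)·(1/2) = 2/3 |
| 4 | 1 | 1 |
| Sum over 4 | 1.333 (33.3%) | 2.833 (70.8%) |

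Chance alone would give 50% correct guesses.

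**Incomplete blocks.** Strata seldom end on a full block, and the unfilled places are the predictable ones, so the figures above are upper bounds. The number of sites is not given. Assuming 4, 8 or 12 sites of equal size (16, 32 or 48 strata), with children spread at random over the strata:

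| Randomised | Sites assumed | Children per stratum | Known with certainty | Best guess correct |
|---|---|---|---|---|
| 137 | 4 | 8.6 | 28.5% | 68.7% |
| 137 | 8 | 4.3 | 23.5% | 66.4% |
| 137 | 12 | 2.9 | 18.1% | 64.0% |
| 400 | 4 | 25.0 | 31.7% | 70.1% |
| 400 | 8 | 12.5 | 30.0% | 69.3% |
| 400 | 12 | 8.3 | 28.3% | 68.6% |

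**What varied block sizes would change.** Simulation of an observer who knows the set of sizes and all past allocations in the stratum, but not where blocks end, for strata of 8 to 24 children:

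| Block sizes | Known with certainty | Best guess correct |
|---|---|---|
| 4 only | 33% | 71% |
| 4, 6 | 5.6–6.1% | 66.8–68.6% |
| 4, 6, 8 | 2.4–3.0% | 66.1–67.3% |

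Best-guess success moves little because betting on the arm that is behind needs no knowledge of block ends. Over complete blocks it is (2.833 + 4.1)/10 = 69.3% for sizes 4 and 6, and (2.833 + 4.1 + 5.329)/18 = 68.1% for 4, 6 and 8. The gain is almost all in certainty.

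**Possible consequence, on assumed bias only.** With 35% improvement in both arms and 170 per group, SE = √(2·0.35·0.65/170) = 0.0517. A bias of 2 percentage points in the difference raises the two-sided type I error from 5% to 6.7%, and 5 points raises it to 16%. If steering acted only on a known third of allocations, those biases would need prognosis gaps of 0.02/(1/3) = 6 points and 0.05/(1/3) = 15 points between the children steered to each arm. The documents do not tell us whether gaps of that size are plausible.

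**How many children a change could protect.** From 21 December 2017 to January 2022 is about 49 months, and 137/49 = 2.8 a month. From publication to the scheduled close is about 8.5 months, so about 24 children at that pace. Against target, at most 400 − 137 = 263.

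**The case against.** The strongest reply is that there is little room to use foreknowledge. At 2.8 children a month over an assumed 16 to 48 strata, one stratum receives a child about every 6 to 17 months (16/2.8 to 48/2.8), and a block takes about 2 to 6 years to fill. There will seldom be a second child of the same age group and laterality at the same site to swap into a predicted place. This stands as a limit on the likely size of any bias. It does not remove the problem: past allocations can be looked up, and encouraging or delaying a single child needs no second child.

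The safeguards also count. A GP confirms eligibility, clinicians or their delegates contact families found through databases, consent precedes randomisation, and consent and eligibility are monitored for every participant. These restrict exclusion once an allocation can be guessed. But the GP is also unblinded, and the choice of whom to approach and when comes before all of these steps except the clinicians' contact, which applies to only one recruitment route.

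A reader might infer more than the documents support:

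- That a third of this trial's allocations were known. The 33% and 71% assume complete blocks and an RO who keeps track.
- That sites knew the block size from the start. The article shows only that it was public from April 2022.
- That the RO alone decides eligibility. The GP confirms it.
- That analysis can do nothing. Bias through age, sex, laterality and site is addressed by the planned adjustment; what remains is bias through other prognostic features.

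**Conclusion.** The point holds as an avoidable weakness in allocation concealment. It follows from rules the article states: one block size, strata that include site, immediate open allocation, and one role that both recruits and randomises. The share of allocations that could be known in advance is at most 33%, and about 18–29% at the 137 randomised under the assumption of 4 to 12 equal sites. Both figures suppose that the RO knows the block size and follows the sequences, which is not established for the period before publication.

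It would be wrong to conclude that selection bias occurred or that the trial is invalid. The document contains no evidence either way, and the type I error figures are illustrations on assumed bias. Because the change is cheap it is worth making, but its benefit may be small: if recruitment closes on schedule at the past pace, about 24 children are affected, of whom at most 24/3 = 8 would have had a determined allocation.

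**What to change.** For all remaining allocations in every stratum, have the randomisation centre load a new list with randomly varied block sizes, for example 4 and 6, or 4, 6 and 8. Withhold the sizes from site and coordinating staff and from public documents until recruitment closes. Withholding is an essential part of the change, since varying the sizes alone leaves best-guess success near 67–69%. Blocks of 2 add little: with 2, 4 and 6, long-run best-guess success is (1.5 + 2.833 + 4.1)/12 = 70.3%.

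The cost is a new list in the telephone system and a maximum within-stratum imbalance of 3 (with blocks of 6) or 4 (with blocks of 8) instead of 2. If unfinished blocks of 4 are dropped at the switch, any imbalance they leave, at most 2, adds to this. The sample size is unchanged.

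For children already randomised, the list cannot be changed. Use the allocation log to compare baseline prognosis by how predictable each child's place in the block was, for example day-0 OMQ-14 score, sex and exact age against the probability of autoinflation given the earlier allocations in that block. With 137 children such a check has limited power, so a null result should not be read as clearance. Report the fixed block size as a limitation in the main paper.
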